### Study duration

The treatment and observation duration of the study is approximately 8 days. The study consists of a 30-day screening period.

#### Inclusion criteria and exclusion criteria

##### Inclusion criteria

Patients must fulfill all of the following criteria to be eligible for the study: 1) male or female patient between 20 and 80 years of age at screening; 2) scheduled to electively undergo open laparotomy; 3) American Society of Anesthesiology physical class 1–3; and 4) ability and willingness to provide informed consent.

##### Exclusion criteria

Any of the following criteria disqualifies the patient from participation: 1) body mass index (BMI) less than 18 kg/m^2^ or greater than 30 kg/m^2^; 2) history of previous open laparotomy; 3) the planned surgery might cause major complications or requirement of blood transfusion (life-threatened level) based on the medical history and current physical condition of the patient; 4) history of hypersensitivity or adverse reaction to local anesthetics, opioids, or any ingredient of the medications administered in this study; 5) severe comorbidity; 6) chronic preoperative opioid consumption; 7) pregnancy or breastfeeding; and 8) inability to use the PCA device.

### Terminations and withdrawals

Patients are advised that they are free to withdraw from the study at any time. The investigator may also withdraw the patient from the study at any time if, for example, patients become ill or their behavior may compromise the outcome of the study. Any withdrawal of patients from the study will be documented in the final report. The decision to stop treatment will be taken by the investigator.

### Study treatment

#### Description of investigational product and the comparator product

Eligible patients will be randomly assigned to receive one of the following treatments: Group 1—Naldebain^®^ injection (150 mg nalbuphine sebacate, 75 mg/mL, 2 ml/vial); Group 2—PCA with fentanyl (not more than 300 μg/day)

### Study drug administration

Group 1 receives an intramuscular single dose of Naldebain^®^ 24 ± 12 h prior to surgery. The suggested injection site is the musculature of the buttocks. Care is taken to ensure that the drug is not injected into the adipose tissue. Group 2 receives intravenous PCA with fentanyl through 48 h postsurgery.

### Packing and labeling

All drugs used in the study are commercially packed and labeled.

### Handling and storage

Naldebain^®^ is stored in a dry place at a temperature of 2–8 °C and kept away from direct light exposure and excessive humidity. The study investigator or the designated pharmacist is in charge of the management and dispensation of the study medications.

### Product accountability

Drug dispensing documentation is maintained by the delegated investigator, nurse, or pharmacist.

### Treatment compliance

Throughout the study the time of study medication administration is recorded using the case report form (CRF) which is reviewed at all study visits.

### Concomitant therapy

All concomitant medication/therapy being taken by patients upon entry into the study and all treatments given in addition to the study medication during the study are regarded as concomitant treatments and are documented.

### Supplemental analgesics

If patients are unable to achieve satisfactory pain relief from the assigned treatments by randomization, supplemental analgesics may be administered. Ketorolac and morphine may be used as supplemental analgesics as required. All such medication has the start date, stop date (if not ongoing), medication name (generic preferred), dose, frequency, route, and reason for use recorded as part of concomitant therapy.

If patients are hypersensitive to Naldebain^®^, immediate intravenous administration of Narcan^®^ (naloxone hydrochloride) is a specific antidote. Oxygen, intravenous fluids, vasopressors, and other supportive measures are used as indicated.

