## Background

### Disease background

Most patients who undergo surgery experience acute postoperative pain; however, evidence suggests that fewer than half of the patients achieve adequate or satisfactory postoperative pain relief [1]. Postoperative pain, especially when poorly managed, leads to harmful acute effects (i.e., adverse physiological responses) and increases the risk of postoperative complications and persistent postoperative pain [2]. Persistent postoperative pain is an intricate response to tissue trauma during surgery that stimulates hypersensitivity of the central nervous system, which causes pain in areas not directly affected by the operative procedure. Either acute or chronic postoperative pain can increase the possibility of postoperative complications, increase the cost of medical care, and complicate wound recovery and subsequent return to normal activities. Pain control following surgery is a major priority for both patients and surgeons.

Several preoperative, intraoperative, and postoperative interventions and management strategies are available for reducing and managing postoperative pain. Opioids and nonsteroidal anti-inflammatory drugs (NSAIDs) are commonly used for postoperative pain management [3]. When given systematically, however, these drugs cause side effects including nausea, vomiting, dizziness, sedation, and pruritus [4]. Opioids can cause respiratory depression, and NSAIDs can impair renal function [5].

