##### Study day 1 (all eligible patients)

Eligible patients are required to check into the clinical site before surgery (day 0). The following procedures are performed at check-in: 1) review inclusion/exclusion criteria; 2) randomization; 3) review of concomitant medications; and 4) review of adverse events (AEs).

Additional laboratory tests are requested as required by the investigator.

All eligible patients are hospitalized and randomized into the two treatment groups: Group 1—intramuscular Naldebain^®^ (150 mg nalbuphine sebacate) 24 ± 12 h before surgery; Group 2—Intravenous PCA with fentanyl through 48 h postsurgery.

For pain assessment, patients in Groups 1 and 2 rate their pain intensity using the VAS pain scale prior to dosing or at day 1, respectively.

Vital signs are checked prior to dosing and once daily until day 6.

Group 1 receives Naldebain^®^, and the injection site is evaluated within 1 h prior to dosing.

##### Study day 0 to 5

All patients are given general anesthesia prior to their scheduled surgical procedure. If patients require additional medication for the treatment of pain, ketorolac and morphine can be used as supplemental analgesics as required. Post-surgery, the following evaluations are performed: 1) for pain assessment, all patients rate their average pain intensity using a VAS pain scale (assessments are performed before the first use of PCA or supplemental analgesics and then at 4 ± 1, 24 ± 2, 32 ± 3, and 48 ± 4 h, and once daily on day 3 to day 5 following surgery); 2) BPI evaluation is performed on day 2; 3) vital signs (temperature, respiratory rate, blood pressure, and heart rate) are examined once daily prior to the final visit; 4) in Group 1 (the IM-Naldebain^®^ group), the injection site is evaluated once daily until the final visit; 5) a review of concomitant medication and adverse events are record; and 6) in Group 2 (the IV-PCA group), the amount of fentanyl used is recorded from day 0 through day 2.

##### Study day 6

The following evaluations are performed at day 6: 1) for pain assessment, patients rate their pain intensity in the patient diary; 2) BPI is evaluated; 3) vital signs (temperature, respiratory rate, blood pressure and heart rate) are examined; 4) the injection site is evaluated; 5) a review of the AE record; and 6) a review of concomitant medication.

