Open abdominal surgery is associated with postoperative pain, nausea, ileus, and prolonged hospital stay with associated costs [17]. Although opioids have been the mainstay of perioperative analgesia, they are significantly associated with postoperative ileus, especially when daily dosing exceeds 2 mg of intravenous hydromorphone equivalents [18]. Fentanyl-based intravenous PCA (IV-PCA) requires a higher dose of opioids to acquire satisfactory analgesic effects. This, in turn, produces adverse effects such as nausea, vomiting, and pruritus, which causes patients to discontinue the use of IV-PCA [19, 20]. Nalbuphine is a semisynthetic opioid indicated for the relief of moderate to severe pain. Its short half-life requires frequent injections in clinical practice, resulting in a greater incidence of AEs. A prodrug of nalbuphine, nalbuphine sebacate, has been developed, dissolved in a simple oil-based injectable formulation that can deliver and maintain an effective blood level of nalbuphine [6]. Tien et al. demonstrated that the complete release of nalbuphine sebacate into the blood stream required approximately 6 days, during which nalbuphine sebacate was rapidly hydrolyzed to nalbuphine; this suggests that a single injection of 150 mg nalbuphine sebacate can provide long-lasting pain relief [6].

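### The naloxone instruction names hypersensitivity to Naldebain as its trigger, which is the wrong event on the ordinary reading and a misnamed one on any reading

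*Protocol article*

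**What the plan says.** The section Supplemental analgesics allows ketorolac and morphine when the assigned treatment does not control pain. It then turns to rescue and states: "If patients are hypersensitive to Naldebain^®^, immediate intravenous administration of Narcan^®^ (naloxone hydrochloride) is a specific antidote". The next sentence adds: "Oxygen, intravenous fluids, vasopressors, and other supportive measures are used as indicated". Naloxone is mentioned nowhere else in the article.

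Four other places bear on how the instruction should be read:

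- Exclusion criteria, item 4: "history of hypersensitivity or adverse reaction to local anesthetics, opioids, or any ingredient of the medications administered in this study".
- Background, Disease background, on persistent pain: "tissue trauma during surgery that stimulates hypersensitivity of the central nervous system".
- Background, Disease background, on the harms of analgesics: "Opioids can cause respiratory depression, and NSAIDs can impair renal function".
- Discussion: "Nalbuphine is a semisynthetic opioid indicated for the relief of moderate to severe pain".

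**The concern.** The sentence tells staff when to give an antidote at once, so its trigger should be the event that the antidote reverses. For an opioid antagonist that event is excessive opioid effect, with respiratory depression as the obvious sign. The sentence names hypersensitivity instead.

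Taken literally, it sends naloxone to an allergic-type reaction, for which it is not a specific treatment, and gives no trigger for the event that naloxone does treat. The omission is relevant in this arm: the single injection cannot be stopped once given, and the same section permits morphine on top of it. At stake is the clarity of a safety instruction, not the validity of the comparison between the groups.

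**Working it through.** There is no figure in the plan to reproduce and no calculation on which the point depends. The check is a comparison of texts.

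**1. Drug class.** The Rationale describes nalbuphine sebacate as a prodrug of nalbuphine, and the Discussion calls nalbuphine a semisynthetic opioid. One premise comes from outside the article: naloxone antagonises opioids. This is general pharmacology and is taken as an assumption.

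**2. Meaning of the trigger.** Apart from the naloxone sentence, the article uses hypersensitivity twice.

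| Place | What the term refers to | Reading it supports |
|---|---|---|
| Exclusion criteria, item 4 | A reaction to local anesthetics, opioids or any ingredient of the medications | Ordinary drug-reaction sense |
| Disease background | The central nervous system after surgical trauma | Exaggerated responsiveness |

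The first is the only other use that concerns a drug. Because it extends to local anesthetics and to every ingredient, it cannot be confined to exaggerated opioid effect. The second concerns a nervous-system response to injury, not to a medicine, so it lends the looser meaning only weak support.

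**3. Each reading taken through the sentence.**

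- *Ordinary drug reaction.* An opioid antagonist is not a specific antidote to an allergic-type reaction, least of all one caused by another component of the oil-based formulation. The trigger is the wrong event.
- *Undue sensitivity to the opioid effect.* The antidote fits. However, the sentence names no clinical sign and uses a word that the exclusion criteria use differently. The trigger is misnamed.

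**4. Is it corrected elsewhere?** No. Respiratory depression appears only in the background section, where it is not linked to naloxone. No section ties naloxone to overdose, sedation or depressed breathing.

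**5. Reach.** 110 patients randomized 1:1 gives 110 / 2 = 55 planned for Naldebain. That is the number to whom the instruction applies, not the number expected to need it. The article gives no rate for hypersensitivity or for excessive opioid effect, and none is assumed here.

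**The case against.** The best defence is that the authors meant excessive opioid effect and chose a poor word. Calling naloxone a specific antidote is the language of countering a drug's action, and the oxygen, fluids and vasopressors that follow are consistent with managing opioid toxicity. The screening section uses a different word, allergies, when it records allergic history, and the exclusion criterion defines neither of its terms. The sentence is also brief and descriptive. It appears in a condensed article, and detailed rescue procedures may well be in the full protocol.

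Much of this stands. The intended meaning is arguable, and the looser reading may well be the intended one. The article contains no internal contradiction either, since no other section says when naloxone should be given. But the defence does not make the wording adequate. The supportive measures would suit an allergic reaction as well as opioid toxicity, so they do not settle the meaning. Nor is this a matter of detail left to a fuller document: the article states a trigger, and the trigger is either the wrong event or the wrong name for the right one.

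A reader might go further and infer that patients with respiratory depression would be denied naloxone, or that allergic reactions would go untreated. The article does not support that. It forbids neither treatment, allows supportive measures as indicated, and keeps patients in hospital: "All eligible patients are hospitalized and randomized into the two treatment groups". Table 1 opens discharge on day 6.

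A reader might also try to build a period of risk from the statement that "the complete release of nalbuphine sebacate into the blood stream required approximately 6 days". That duration describes exposure to the drug. It does not measure the consequence of a misnamed trigger.

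**Conclusion.** The point holds as a minor one. On the ordinary drug-reaction sense of hypersensitivity, the article gives the wrong event as the trigger for an opioid antagonist. If excessive opioid effect was intended, the trigger is misnamed and its main sign is left out. The wording needs correcting either way, so the conclusion does not depend on which meaning was intended.

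The documents do not justify calling the sentence wrong on every reading, or calling it a demonstrated hazard. The practical risk is small, and the number of patients affected cannot be derived. No endpoint, sample size or analysis changes. The one assumption is the uncontroversial premise that naloxone acts by reversing opioid effect.

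**What to change.** Replace the sentence with two separate rules:

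1. If a patient who has been given Naldebain, with or without supplemental morphine, shows signs of excessive opioid effect such as respiratory depression, give intravenous naloxone immediately as the specific antidote.
2. If a patient has a hypersensitivity reaction to Naldebain, treat it as an allergic reaction, with the supportive measures already listed, as indicated.

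State that those supportive measures are available for both events.

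Two details matter. Simply swapping the trigger would delete the article's only words on managing hypersensitivity to Naldebain, so the second rule is needed. The first rule should also not require staff to attribute the effect to Naldebain, because these patients may have received morphine as well and the source may not be separable at the bedside.

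The cost is one or two sentences, with no new procedure, case report form field or analysis. Trial status gives an expected finish of December 2018 and the article appeared in March 2019, so the benefit may lie mainly in correcting the record and any later document that reuses the wording.

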### Study assessments and procedures (see Table 1)

#### Schedule of assessments

##### Screening (days −30 to −1; all study patients)

The nature of the study, as well as the potential risks and benefits associated with study participation, are fully explained to all potential patients. The following are obtained: 1) informed consent; 2) demographic information, including sex, age, BMI, and type of surgery; 3) vital signs, including temperature, respiratory rate, blood pressure, and heart rate; 4) medical history, including medication use and any history of allergies; 5) physical examination; 6) laboratory testing, including hematological and biochemical tests, and urinalysis; 7) electrocardiogram (ECG) and x-ray; and 8) BPI is evaluated at day –1.

**Table 1 Tab1:** Study event flowchart

Period	Screening	Study period						
Study day	−30 to −1	−1	0	1	2	3–5	6	Discharge
Informed consent	X							
Medical history	X							
Demographic data	X							
Physical examination	X							X
Vital signs	X	X	X	X	X	X	X	X^d^
Injection site evaluation		X^b^	X^b^	X^b^	X^b^	X^b^	X^b^	X^b,d^
Laboratory tests	X	X^a^						X
12-lead ECG/chest x-ray	X							
Inclusion/exclusion criteria		X						
Randomization		X						
Naldebain^®^ administration		X^b^						
Surgery			X					
Pain assessment		X	X	X	X	X	X	
BPI		X			X		X	
Patient satisfaction								X
Concomitant medication	X	X	X	X	X	X	X	X^d^
Adverse event record		X	X	X	X	X	X	X^d^
Drug accountability for fentanyl			X^e^	X^e^	X^e^			
Discharge								X^c^
End of study								X

*BPI* brief pain inventory, *ECG* electrocardiogram

^a^Additional laboratory tests are requested as required by the investigator

^b^Only for subjects who are randomized to the Naldebain^®^ group

^c^Patients can discharge on day 6–30; patients still hospitalized after day 6 do not serve as a protocol deviation/violation or serious adverse event

^d^For patients who are discharged on day 6, the assessment is performed only once

^e^Only for subjects who are randomized to the patient-controlled analgesia (PCA) group

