##### Final visit (discharge, day 6–30)

For safety concerns, the study will follow-up each patient until discharge (within a time window for discharge of 6–30 days). The patients will be evaluated for: 1) vital sign (temperature, respiratory rate, blood pressure, and heart rate) examination; 2) injection site evaluation; 3) laboratory tests, including hematological and biochemical tests, and urinalysis; 4) patient satisfaction (at the final visit, each patient is asked the following question (Table 2): “How satisfied were you with your postsurgical analgesia?” and patients are asked to classify themselves as either “highly satisfied,” “satisfied,” “uncertain,” “dissatisfied,” or “very dissatisfied”); 5) physical examination; 6) review of the AE record; and 7) review of concomitant medication.

**Table 2 Tab2:** Five-point rating of patient satisfaction

Rating	Description
1	Highly satisfied
2	Satisfied
3	Uncertain
4	Dissatisfied
5	Very dissatisfied

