#### Adverse events

An AE is any untoward medical occurrence in a patient administered the study drug that does not necessarily have a causal relationship with the treatment. An AE can be any unfavorable and unintended sign, symptom, or disease temporally associated with the use of the study drug, regardless of whether it is considered to be related to the study drug. This includes any newly occurring event or previous condition that has increased in intensity or frequency since the administration of the study drug. Lack of efficacy before the study end is not considered an AE.

A serious AE (SAE) is defined as an AE that meets any of the following criteria (Table 4): 1) results in death; 2) is life threatening; 3) results in inpatient hospitalization or prolongation of existing hospitalization; 4) results in a persistent or significant disability/incapacity; 5) results in congenital anomaly/birth defect; and 6) an important medical event.

**Table 4 Tab4:** Severity categories of adverse events

Severity	Description
Mild	Event may be noticeable to patient; does not influence daily activities; usually does not require intervention
Moderate	Event may be of sufficient severity to make patient uncomfortable; performance of daily activities may be influenced; intervention may be required
Severe	Event may cause severe discomfort; usually interferes with daily activities; patient may not be able to continue in the study; treatment or other intervention usually required
Serious	Results in death or life-threatening situation; inpatient hospitalization or prolongation of existing hospitalization; persistent or significant disability/incapacity; or congenital anomaly/birth defect or important medical event

The investigator evaluates the intensity of each AE using the following definitions (Table 4):

Mild—event may be noticeable to the patient; does not influence daily activities; usually does not require intervention.

Moderate—event may be of sufficient severity to make patient uncomfortable; performance of daily activities may be influenced; intervention may be required.

Severe—event may cause severe discomfort; usually interferes with daily activities; patient may not be able to continue in the study; treatment or other intervention usually required.

After careful consideration, the investigator evaluates the relationship of each AE to the study drug by applying the following definitions (Table 5):

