#### Adverse event reporting

All AEs, regardless of causality, that occur between the time the study medication is administered and completion of the treatment phase are reported. Those meeting the definition of SAEs are reported using the SAE form.

All AEs, regardless of seriousness, severity, or presumed relationship to the study drug, are recorded using medical terminology in the source document and the CRF. Whenever possible, diagnoses are given when signs and symptoms are due to a common etiology (e.g., cough, runny nose, sneezing, sore throat, and head congestion should be reported as “upper respiratory infection”). Investigators must record in the CRF their opinion concerning the relationship of the AE to study therapy. All measures required for AE management must be recorded in the source document and according to sponsor instructions.

The investigator must report all such events to the appropriate independent ethics committee (IEC)/institution review board (IRB) that approved the protocol unless otherwise required and documented by the IEC/IRB.

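### Table 1 footnote c exempts stays beyond day 6 from SAE status whatever their cause, which on a literal reading conflicts with the prolonged-hospitalization criterion for an SAE

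*Protocol article*

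**What the plan says.** Footnote c hangs on the Discharge row of Table 1 (Study event flowchart). It opens with the window, "Patients can discharge on day 6–30", and continues that "patients still hospitalized after day 6 do not serve as a protocol deviation/violation or serious adverse event". Nothing in it refers to the cause of the longer stay.

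The Adverse events section states: "A serious AE (SAE) is defined as an AE that meets any of the following criteria". The third criterion is that the event "results in inpatient hospitalization or prolongation of existing hospitalization". Table 4 repeats this in its row for serious events. Neither place mentions day 6.

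Adverse event reporting then sets two duties. The first is general: "All AEs, regardless of seriousness, severity, or presumed relationship to the study drug, are recorded" in the source document and the CRF. The second depends on seriousness: "Those meeting the definition of SAEs are reported using the SAE form". The Serious adverse events section adds transmission to the sponsor and follow-up of unresolved events, and the Safety analysis section adds tables of SAE incidence.

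**The concern.** Every patient is an inpatient, and discharge may fall anywhere in a window of more than three weeks. The article gives no expected length of stay, so footnote c is its only statement on how a stay past day 6 bears on SAE status. As worded, that statement is an unconditional exemption placed in the schedule table.

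The situation is foreseeable. The Discussion links open abdominal surgery with nausea, ileus and longer stays, and links opioids with postoperative ileus. A complication of that kind could delay discharge past day 6 without being life-threatening. Its seriousness would then turn on the criterion that the footnote appears to switch off.

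At stake is the classification of such events, and with it the reporting steps that only serious events trigger.

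**Working it through.** No figure is involved, so the check is a comparison of texts.

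**Step 1: what each rule applies to.** The footnote speaks of patients who remain in hospital after day 6. The SAE definition speaks of AEs that meet a criterion. Under that definition, a stay with no AE behind it can never be an SAE.

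**Step 2: apply both rules to the possible cases.**

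| Case | SAE definition (Adverse events, Table 4) | Footnote c, read literally | Agree? |
|---|---|---|---|
| Stay past day 6, no AE | Not an SAE | Not an SAE | Yes |
| Stay past day 6, AE present that neither prolongs the stay nor meets another criterion | Not an SAE | Not an SAE | Yes |
| AE prolongs the stay past day 6, no other criterion met | SAE | Not an SAE | **No** |
| AE prolongs the stay past day 6 and meets another criterion (for example, life-threatening) | SAE | SAE through the other criterion; the footnote concerns only the stay | Yes |

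The mention of SAEs in the footnote changes a classification only in the third case. In the first two it repeats what the definition already implies.

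**Step 3: follow a third-case event that a site calls non-serious.**

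- *Recording in source and CRF:* still required, because this duty holds regardless of seriousness.
- *Count as treatment-emergent:* unchanged. The Safety analysis section defines this by onset or worsening relative to study drug, not by seriousness.
- *AE review to the end of the stay:* still done. Under Final visit, "the study will follow-up each patient until discharge", and Table 1 marks the AE record in the Discharge column.
- *SAE form:* missed.
- *Transmission to the sponsor by SAE form:* missed.
- *SAE follow-up until resolution or another listed end point:* missed.
- *SAE incidence tables:* the event is absent.

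**Step 4: a limit on the reassurance in step 3.** Adverse event reporting covers events that "occur between the time the study medication is administered and completion of the treatment phase are reported". The article does not define when that phase ends. For an AE that begins late in a long stay, recording therefore rests on the review at discharge.

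**The case against.** The best reply is that the passages can be read together. The footnote belongs to the Discharge row, and its second half follows from the window in its first half: because discharge is allowed up to day 30, being in hospital on day 7 is not an event to log. The footnote does not claim to amend the SAE definition, and the trigger for the SAE form is the definition. The article also condenses a fuller protocol, and site instructions on SAEs may sit there.

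Most of this stands. The narrow reading is probably the intended one, and how sites would act cannot be inferred from the footnote alone. But the footnote does not state the limit that the narrow reading needs, and the one case in which its words alter a classification is the case in conflict.

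A reader might infer that AEs which prolong a stay would go unreported. The documents do not support that: every AE must be recorded whatever its seriousness, and AE review continues to discharge. Length of stay is also a secondary efficacy endpoint, so a long stay is captured, although that endpoint does not record its cause.

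A reader might also infer damage to the safety comparison, since safety is part of the primary objective. The stated safety endpoints are the incidence of treatment-emergent AEs and abnormalities in vital signs, laboratory tests and injection sites. None of these depends on seriousness, and the SAE summaries are descriptive.

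**Conclusion.** The inconsistency is real but minor. Read literally, footnote c and the SAE definition disagree on one class of event: an AE that prolongs the stay past day 6 and is serious on no other ground. The consequence is possible under-classification of seriousness, which affects the SAE form, transmission to the sponsor, SAE follow-up and the SAE tables.

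Its size cannot be given. The article states no rate of stays beyond day 6 and no rate of AEs that cause them, so any count of affected patients would be guesswork. Nor is there support for the inference that differing site readings would add noise to the comparison between arms.

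The conclusion assumes that a site might take the footnote as an operative exemption. It also assumes that nothing in the fuller protocol or the sponsor's instructions already limits the footnote.

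**What to change.** Reconcile the two passages by adding a limit to footnote c. For example: *Remaining in hospital after day 6, within the day 6–30 window, is not in itself a protocol deviation or an SAE; an AE that prolongs hospitalization remains subject to the SAE definition under Adverse events.* Tell the sites of the clarification. The SAE definition and Table 4 need no change.

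The cost is one clause, a short notice to sites and possibly a few more SAE forms. Treatment, the discharge window, the assessments and the analyses are unaffected, and the footnote's likely purpose is kept.
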